### Statistical analyses

Baseline characteristics of the two groups will be presented as means/medians or proportions and their 95% confidence intervals and compared using *t*-tests for normally distributed data, using chi-square tests for proportions and the appropriate non-parametric methods for non-normally distributed data. Baseline demographic and clinical characteristics for those who do and do not withdraw will also be completed. A secondary analysis to re-present the primary results for each of the strata (<1 year and >1 year) will be done to account for the stratification.

For our primary aim, agreement between OPA determined clinical and MBS assessments will be calculated using percent agreement and a kappa coefficient. All evaluable data will be used minus the 8% of dropouts. Taking MBS determination of presence or absence of OPA as the gold standard, sensitivity, specificity, negative predictor value (NPV), positive predictor value (PPV), pretest probability and likelihood ratios will also be calculated. Likelihood ratios will also be calculated.

For our secondary aim, categorical variables of pre-, during and post-swallowing sound parameters will be analysed using a chi-square test to determine which sound qualities are significantly associated with OPA. Multivariate regression analysis will be used to determine whether age, gender, texture, method of intake or clinician level of experience are independent predictors associated with the absence/presence of OPA. All variables will be analysed univariably, then include all those with *p* < 0.15 in a multivariable model. Forward stepwise regression modelling will be employed to identify variables independently associated with OPA and account for interaction effects. The *a priori* statistical level of significance is *p* < 0.05. Missing data points will be coded as a number on the database and analysis completed on the remaining data.

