### Randomisation

A computer-generated simple randomisation list, stratified by age (<1 year or ≥1 year), was produced by an external statistician. Allocation concealment will be maintained by group allocation (i.e. CFE or CFE + CA) being concealed in sequentially numbered, opaque envelopes until after consent and baseline information has been obtained. The envelope is opened in front of the treating speech pathologist and caregiver prior to the commencement of their feeding examination.

We stratified by age because swallowing function is influenced by age. The cutoff of 12 months was chosen based on two factors: (1) the swallow-respiration pattern changes at 1 week and between 6 to 12 months of age [34]; (2) anatomical maturity that occurs at approximately 12 months that impacts on a child’s ability to feed more efficiently [35]. These maturity factors include fusion of the mandible halving to improve jaw grading ability, fat pads reducing to increase the oral cavity size and the position of the trachea being more vertical in toddlers than infants.

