## Discussion

Assessment of oropharyngeal dysphagia is the most common reason for referral to speech pathologists in tertiary paediatric hospitals. OPA, if left unmanaged, may result in substantial acute and chronic respiratory morbidity [4]. Current diagnostic techniques are limited by accessibility and cost. CA is a tool that potentially improves the clinical assessment of children with oropharyngeal dysphagia at risk of OPA, particularly in regions where MBS is not readily available. This unique study will therefore inform the clinical care and management of children with oropharyngeal dysphagia.

Using CA is dependent on sound differentiation. The link between perceptual and acoustic sound parameters to differentiate between normal and abnormal swallow sounds has been described in three studies that used different parameters [54,57,58]. Rommel et al. [54] collected perceptual and acoustic swallow parameters on 17 healthy children and 9 children with OPA. They defined perceptual swallowing parameters as “abnormal” (flushing sound of liquid heard prior to swallow, coughing or throat clearing after the swallow and/or laryngeal stridor) or “normal” (clear breath sounds heard after the swallow during post-swallow inspiration or expiration) [54]. Statistically significant differences in acoustic parameters of peak amplitude (ranges 16, 25) (*p* < 0.0001) and relative amplitude fundamental frequency (means −11, -16) (*p* < 0.05) data between normal and abnormal perceptual swallow sounds were reported. However, the study had several limitations including a small sample size (*n* = 26), poor matching between groups (children were not age-matched, which is important as age influences swallowing function), and limited data on different viscosities and textures with only thin fluids data reported. Further data on acoustic and perceptual parameters of swallowing on a variety of food and fluid consistencies are required to see if this result is generalisable to other consistencies, apart from thin fluids.

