Vice et al. [57] described different sound types in swallowing on a study that evaluated six healthy newborn (within the first 2 days post delivery) infants. They found that the initial discrete sound (IDS) heard at the beginning of the bolus transit sound (BTS) became more uniform with increasing age [57]. Swallow sounds were recorded using an accelerometer and subsequently transferred on to a signal file manager. From these files, waveforms of the swallow sound against time (seconds) and amplitude (volts) were obtained. The IDS was consistently objectively identified from the swallow waveform [57]. Study limitations included a small sample size and unclear definitions. In another study, accelerometer recorded swallow sounds, which were converted to waveforms via a signal file manager, demonstrated waveform shape differences on initial discrete sounds between pre-term infants with and without chronic neonatal lung disease (CNLD) [57,58]. The shape of the waveform or “variance index” in infants with CNLD was significantly different from that in infants without CNLD.

Despite the limitations of the three studies above, they provided proof of concept. Perceptual parameters of swallowing sounds can be linked to objective acoustic data in infants and young children and a differentiation between normal and abnormal swallows is possible perceptually and acoustically. Our study has therefore been designed to build upon previous CA research and addresses the limitations of those studies.

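### The plan names swallow sounds as associated with OPA by an unadjusted chi-square test and does not secure adjustment for age or texture

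*Protocol article*

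**What the plan says.** All of the analysis text on this point is in the Statistical analyses section of the protocol article, in the paragraph on the secondary aim.

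- **Sounds.** The pre-, during and post-swallow "sound parameters will be analysed using a chi-square test to determine which sound qualities are significantly associated with OPA". No covariate or stratum is named.
- **Regression.** A separate sentence asks "whether age, gender, texture, method of intake or clinician level of experience are independent predictors associated with the absence/presence of OPA". No sound parameter is in that list.
- **Model building.** "All variables will be analysed univariably, then include all those with" p < 0.15 in a multivariable model, and then "Forward stepwise regression modelling will be employed to identify variables independently associated with OPA and account for interaction effects". The text does not say whether the sounds are among these variables.

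The re-presentation of results by age stratum, earlier in the same section, covers only the primary results.

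Elsewhere the article treats age as important. The Randomisation section says "We stratified by age because swallowing function is influenced by age". The Discussion faults an earlier paediatric sound study because "children were not age-matched, which is important as age influences swallowing function". It later states, after reviewing three such studies: "Our study has therefore been designed to build upon previous CA research and addresses the limitations of those studies".

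**The concern.** The secondary aim is to learn which sounds go with OPA. Eligibility covers all children under 18, and the foods and fluids offered depend on age (Table 1). A sound that is simply commoner in infants will look associated with OPA wherever OPA is also commoner in infants, even if the sound says nothing about aspiration in a child of given age. The same can happen with texture if child-by-texture records are pooled. Confounding in the other direction could hide a sound that is informative.

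The article expects its results to influence clinical practice, so a list of sounds of OPA is likely to be used. Taken literally, the test named for producing that list has the lack of age control that the Discussion criticises in earlier work.

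**Working it through.** **1. Is there a stated figure to reproduce?** None for the sound analysis. The only sample size, 108 per group in the Sample size section, is for the primary comparison. It matters here because the perceptual parameters are collected in the CFE + CA group only, so about 108 children contribute.

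**2. What does the text secure?** There are two readings.

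| Reading | Test that decides on a sound | Age and texture in the model? |
|---|---|---|
| The sounds are outside the regression list | Crude chi-square | No |
| The sounds are among all variables screened | Chi-square as screen, then stepwise model | Only if each passes p < 0.15 and is then selected |

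Neither reading fixes adjustment in advance.

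**3. How large could the effect be?** The documents give no OPA or sound frequencies by age or texture, so every rate below is an assumption. Take two equal age groups and a sound that is independent of OPA within each group. With OPA rates o₁, o₂ and sound rates s₁, s₂:

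- P(sound | OPA) = (o₁s₁ + o₂s₂) / (o₁ + o₂)
- P(sound | no OPA) = [(1 − o₁)s₁ + (1 − o₂)s₂] / [(1 − o₁) + (1 − o₂)]

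Worked case, OPA 20% and 40%, sound 30% and 60%:

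- P(sound | OPA) = (0.06 + 0.24) / 0.60 = 0.50
- P(sound | no OPA) = (0.24 + 0.36) / 1.40 = 0.429
- Crude odds ratio = (0.50/0.50) / (0.429/0.571) = 1.33, although the true within-group odds ratio is 1.

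Simulated false-positive rates at a two-sided 5% level, N = 108, groups expected to be equal (20,000 runs, except † 4,000 runs):

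| Assumed confounding | OPA in the two groups | Sound in the two groups | Crude OR | Crude chi-square | Stratified (Mantel-Haenszel) |
|---|---|---|---|---|---|
| None | 30%, 30% | 30%, 60% | 1.00 | 5.1% | 4.8% |
| Weak | 25%, 35% | 40%, 60% | 1.10 | 5.7% | 4.8% |
| Moderate | 20%, 40% | 30%, 60% | 1.33 | 10.8% | 4.8% |
| Moderate† | 15%, 35% | 25%, 50% | 1.3 | 10% | about 5% |
| Moderate† | 15%, 40% | 25%, 60% | 1.6 | 20% | about 5% |
| Strong | 15%, 45% | 20%, 70% | 2.06 | 40.6% | 5.0% |
| Very strong | 10%, 50% | 20%, 70% | 2.64 | 62.7% | 4.9% |

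The first row shows the condition for bias: the factor must be related to both the sound and OPA. If it is related to the sound alone, the crude test keeps its level.

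**4. What if the sounds do enter the stepwise model?** Simulating that procedure with one irrelevant sound and age as the only candidates (screen at p < 0.15, entry at p < 0.05):

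- OPA 35% and 15%: age passes the screen in about 85% of runs, and the sound ends in the final model in 5.0%.
- OPA 40% and 15%: age passes in about 95%, and the sound is retained in 4.2%.

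In this small setting the stepwise route largely removes the excess. Age is still screened out in about 15% and 5% of runs respectively, so adjustment is usual but not assured.

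**The case against.** The strongest reply is that adjustment is already planned. The multivariable model stands in the same paragraph, under the same secondary aim, and contains age and texture. If the sounds are among the variables screened, the chi-square is only a first step, and the check above shows error near 5% in the scenarios tried. That stands as far as it goes. It depends on a phrase that does not mention the sounds, against a list that leaves them out, and it was tested with only two candidates; a model with many sounds and covariates could behave differently.

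Four further limits also stand.

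- **Texture.** A reader might infer that the protocol names texture, like age, as a driver of swallowing. It does not. The Background reports different CFE sensitivity on fluids and solids, and the Discussion says that data on other consistencies are needed. Nor does it say that the chi-square pools textures. OPA is judged per texture (Outcome measures), so a test within each texture is equally compatible with the text.
- **Earlier studies.** A reader might infer that the trial repeats every limitation it criticises. It does not: it has a larger sample, a definition sheet and several textures. Only the lack of age control recurs, and only if the chi-square decides.
- **Sounds and age.** The Discussion reports that the initial discrete sound changes with age, but in six newborns studied within two days of delivery. That does not show a difference between children under and over one year.
- **Descriptive aim.** The secondary aim is largely descriptive, and a marginal association is legitimate as description. An analysis plan that is not shown may also give the model in full. However, the article does state a test and says that it will determine which sounds are significantly associated, so the choice can be judged as stated.

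**Conclusion.** The point holds in a limited form. The only test tied by name to the sounds is unadjusted, the regression list omits them, and on either reading adjustment for age and texture is not guaranteed. Since the protocol itself holds that age influences swallowing, a sound that tracks age could be reported as a sound of OPA; so could one that tracks texture, if records are pooled over textures.

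The size cannot be derived from the documents. Under assumed frequencies with 108 children, the false-positive rate per sound is about 5–6% with weak confounding and 10–20% with moderate confounding, against about 5% when stratified. The higher rates in the table need large differences in both OPA and sound frequency, which nothing in the documents supports. A reader might infer that the trial will publish false signs of aspiration. The documents show only that the stated test does not protect against it.

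This affects a secondary aim and leaves the primary comparison untouched. The change is worth making because it is cheap and uses data already collected.

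**What to change.** - Keep the chi-square tests as description only.
- Base the naming of OPA-associated sounds on a logistic model of MBS-defined OPA on each sound, with age stratum and texture forced in regardless of p-value.
- Where a child contributes several textures, allow for the repeated records with GEE or cluster-robust standard errors. A stratified test that treats the records as independent is not enough: with assumed within-child correlation (random-effect SD 1.5 to 2.5), Mantel-Haenszel stratified by texture rejected in 6–9% of simulated null datasets.
- Report adjusted odds ratios with 95% confidence intervals.
- State whether the sounds also enter the stepwise model.

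**Cost.** A few sentences in the Statistical analyses section and no new data, since age and texture are already recorded. Intervals will be slightly wider, and estimates for rare sounds may be unstable.

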**Table 1 T1:** **Standard presentation of food and fluids during CFE, CFE** + **CA or MBS**

**Age**	**Food and fluid**
4 – 6 months	● Puree
	● Thin fluids via breast or bottle feeding
8 – 12 months	● Puree
	● Lumpy mash
	● Thin fluids via breast, bottle or spout cup
1 – 18 years	● Puree
	● Lumpy mash
	● Chewable solids (biscuit)
	● Thin fluids via breast, bottle or open cup

Three bites or sips of food or fluid are consistent with normative data obtained previously in adults [41,42] and allow for variations in normal swallowing [32,43]. However, the protocol can be modified at the discretion of the speech pathologist depending on the presentation of the child’s observed feeding and swallowing skills. Reasons for potential protocol modification include:

● Suspected OPA on thin fluids, requiring presentation of thickened fluids prior to thin fluids

● Significantly delayed chewing skills, requiring elimination of an age-appropriate solid consistency

● Reduced compliance from the child, requiring early termination of the session

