#### Outcome measures

PAS [23,46,47] scores will be used to objectively determine presence or absence of OPA on MBS, with a score of 6–8 indicating OPA. For CFE, one or more ticked clinical signs of OPA (cough, gagging, voice changes, colour changes, unable to initiate swallow, abnormal laryngeal elevation, oxygen desaturation, eye tearing, multiple swallows, choking, wet breathing, laboured breathing, fremitus, snuffly nose/stertor) [5,12-14,35,49-53] and clinician decision (yes/no) for suspected OPA. For CFE + CA, evaluation was as for CFE outcome measurements and clinician decision (yes/no) for suspected OPA based on pre-, during and post-swallow sound parameters, as listed in Table 2. Presence or absence of OPA is determined by the clinician across all observed swallows for each given texture/consistency in the CFE and MBS. Presence of OPA need only occur once for a child to be marked positive for OPA on that consistency/texture.

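### Texture and method of intake are entered as separate predictors of OPA, but Table 1 gives a method only for thin fluids, so stepwise selection can credit method with an effect of texture

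*Protocol article*

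**What the plan says.** The article's Statistical analyses section sets out a regression under the secondary aim: "Multivariate regression analysis will be used to determine whether age, gender, texture, method of intake or clinician level of experience are independent predictors" of the absence or presence of OPA. Each variable is first tested alone, and those with p < 0.15 go forward. Then: "Forward stepwise regression modelling will be employed to identify variables independently associated with OPA and account for interaction effects".

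The Outcome measures section scores OPA separately for each consistency: "Presence of OPA need only occur once for a child to be marked positive for OPA on that consistency/texture". Texture can be a predictor only if the rows are texture-level results within a child, so that is how the model is read here.

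Table 1 fixes which combinations of age, texture and method occur:

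- 4-6 months: puree; "Thin fluids via breast or bottle feeding".
- 8-12 months: puree and lumpy mash; "Thin fluids via breast, bottle or spout cup".
- 1-18 years: puree, lumpy mash and chewable solids; "Thin fluids via breast, bottle or open cup".

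No method of intake is named for any solid. The text below the table lets the speech pathologist depart from it, for example by giving thickened fluids first.

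**The concern.** Two predictors can be called independent only if the data contain rows in which one varies while the other is held fixed. Under Table 1, any row with a drinking method is a thin-fluid row, and any thin-fluid row has a drinking method. The fluid-versus-solid part of texture and the drinking-versus-eating part of method are therefore the same variable under two names.

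In a model that always held both, this would be a nuisance of coding. In forward selection it decides the result. Both factors carry the same signal, whichever shows the smaller p-value enters first, and the other then has little left to add. A report that method of intake independently predicts OPA, when only the consistency mattered, would misdirect how clinicians read the result.

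**Working it through.** The plan gives no figure for this model, so there is none to reproduce. The check uses Table 1 alone.

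**Cells.** Counting each age-texture-method combination: 4-6 months has puree plus thin fluid by 2 methods = 3; 8-12 months has 2 solids plus 3 methods = 5; 1-18 years has 3 solids plus 3 methods = 6. Total 14.

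**Coding.** Texture has 4 levels (3 indicators). Method has 4 drinking methods plus one shared code for solids (4 indicators). Age has 3 bands (2 indicators). The shared code is an assumption, since Table 1 names no method for solids.

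**The alias.** In every cell, thin = breast + bottle + spout cup + open cup.

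| Model (with intercept) | Columns | Rank | Aliases |
|---|---|---|---|
| Age + texture | 1+2+3 = 6 | 6 | 0 |
| Age + method | 1+2+4 = 7 | 7 | 0 |
| Texture + method | 1+3+4 = 8 | 7 | 1 |
| Age + texture + method | 1+2+3+4 = 10 | 9 | 1 |
| Thin fluids only: age + method | 1+2+3 = 6 | 6 | 0 |

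Adding age to texture plus method adds two columns and two ranks, so age causes no aliasing. Coding age as under 1 year versus 1 year and over also leaves one alias (9 columns, rank 8).

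**Sensitivity to coding.**

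- Giving chewables their own method code: texture + method has 9 columns and rank 7; with age, 11 columns and rank 9 (two aliases).
- Adding thickened fluids by bottle or cup: 11 columns, rank 10 (one alias).
- Also giving thin fluid by the method used for solids, which is outside Table 1: 11 columns, rank 11 (no alias).

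**What stepwise entry does with it.** With one code for solids, the joint texture-method space has 7 - 1 = 6 degrees of freedom. If texture enters first it uses 3, and method can add 6 - 3 = 3, the contrasts among the four drinking methods. If method enters first it uses 4, including fluid versus solid, and texture can add only 6 - 4 = 2, the contrasts among solids. When the only real difference is thin fluid versus the rest, either factor captures it and the other adds nothing true.

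**Simulation.** 216 children; OPA depends on texture only; assumed rates 20-25% on thin fluid and 8-10% on other textures; assumed age and method mixes. None of these rates or mixes is in the protocol.

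- With 1,000 trials per scenario and rows treated as independent, method reached p < 0.05 alone in 78-100% of trials.
- In the same runs, method entered before texture in 9-20% of trials with separate codes for solids and in 23-33% with one code.
- In a further simulation under the same assumed OPA rates, method was kept in the final stepwise model in 11-32% of trials, almost always with texture left out.

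**Age by texture.** There are 3 × 4 = 12 cells. Three are empty: lumpy mash and chewables at 4-6 months, chewables at 8-12 months. Nine occupied cells less 6 main-effect parameters leave 3 of the (3-1) × (4-1) = 6 interaction terms estimable. Spout cup and open cup each occur in one age band, so their contrasts with breast or bottle assume no age-by-method interaction across bands.

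**The case against.** The strongest reply is that this is a coding detail in a secondary model. A redundant column leaves the fit unchanged and software drops it. Factor levels and nested terms are commonly left to an analysis plan, and this is a condensed article. Method of intake is never defined, so restricting it to fluids is compatible with the text, and feeding at the clinician's discretion could break the alias.

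Part of this stands. The model is secondary, the simulation rates are assumed, and in most simulated trials method did not displace texture. The rest does not remove the problem. The article itself fixes the predictor list and forward selection, and selection does not pass through the full model in which redundancy would be harmless. Of the variants tried, the alias disappeared only when a fluid was also taken by the method used for solids, which Table 1 does not provide for.

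A reader might infer more than the document supports:

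- *That texture is nested in age, so none of the three can be separated.* Puree and thin fluids occur in all bands and lumpy mash in two; age + texture has full rank.
- *That a bottle-versus-cup finding is really fluid versus solid.* Both are thin-fluid methods, and their contrast does not involve solids.
- *That two coefficients are always lost.* The second loss needs a separate method code for chewables.
- *That all solid rows drop out, because "Missing data points will be coded as a number on the database and analysis completed on the remaining data".* Each child has one thin-fluid row among 2, 3 or 4 textures, so the loss would be 1/2, 2/3 or 3/4 of rows. But that needs method to be blank for solids and a not-applicable entry to count as missing. The article says neither.

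**Conclusion.** The concern holds in a limited form. If feeding follows Table 1, a thin-fluid effect and an overall drinking-method effect are one quantity, and the model cannot say which of the two predicts OPA. With one method code for solids this is a single exact alias (rank 7 of 8), and it does not depend on sample size or event rates.

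How often the planned selection would name method when only texture matters does depend on assumptions: about 11-32% of simulated trials under the OPA rates and feeding mixes above, varying with coding. Age remains separable from both factors, and breast, bottle, spout cup and open cup can be compared with one another, subject to the single-band limits on the two cups. Only the secondary-aim regression is affected. The primary comparison of diagnostic accuracy and the sample size are not.

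**What to change.** Replace the single predictor list with two statements. First, fit texture across all texture-level rows, with age and the other covariates but without method of intake. Second, test method of intake only within fluid rows, adjusted for age; within thin fluids this model has full rank (6 of 6). An equivalent alternative is one combined factor, with each solid as a level and thin fluid split by method. In either case, limit age-by-texture interactions to cells that occur in Table 1, and state how method is recorded for solids so that a not-applicable entry is not handled as missing.

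The cost is a change of wording before analysis, with no new data. What is given up is a separate method effect across solids, which the design cannot estimate in any case.

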### Aims of the study

Our study investigates the utility of cervical auscultation (CA) in the assessment and diagnosis of OPA in children. The primary aim is to determine whether the CFE combined with CA increases the detection of OPA determined by MBS, compared to the CFE only. We hypothesise that the use of CA (compared to not using CA) as an adjunctive clinical tool to assess oropharyngeal dysphagia improves the detection of OPA in children as assessed with the current gold standard, MBS.

Our secondary aim is to determine the perceptual characteristics of common typical respiratory and swallow sound patterns and/or descriptors pre- and post-swallow in children with OPA.

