#### Perceptual parameters (CFE + CA group only)

Perceptual parameters for sounds heard throughout the pre-swallow, swallow and post-swallow phases are listed in Table 2.

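### Secondary aim: five pre-named covariates for OPA go through a p < 0.15 screen and forward stepwise selection with unnamed interactions; separately, 27 sound entries are tested unadjusted

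*Protocol article*

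**What the plan says.** The secondary aim (Aims of the study) is to "determine the perceptual characteristics of common typical respiratory and swallow sound patterns and/or descriptors pre- and post-swallow in children with OPA". The Statistical analyses section of the protocol article assigns two analyses to it.

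- **Sounds.** The pre-, during and post-swallow sound parameters "will be analysed using a chi-square test to determine which sound qualities are significantly associated with OPA". The section on perceptual parameters, whose heading limits it to the CFE + CA group, says: "Perceptual parameters for sounds heard throughout the pre-swallow, swallow and post-swallow phases are listed in Table 2". Table 2 has nine entries in each of three columns.
- **Covariates.** A regression is to determine "whether age, gender, texture, method of intake or clinician level of experience are independent predictors associated with the absence/presence of OPA". The route to the model is: "All variables will be analysed univariably, then include all those with *p* < 0.15 in a multivariable model". Then: "Forward stepwise regression modelling will be employed to identify variables independently associated with OPA and account for interaction effects".

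One threshold is given for everything: the a priori "statistical level of significance is *p* < 0.05". The section states no adjustment for the number of sound tests, does not call either analysis exploratory, and names no interaction. The Discussion mentions interaction models for the interval between clinical examination and MBS, but that interval is not one of the five covariates.

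Under Outcome measures, OPA is marked positive or negative per consistency or texture. Under Modified Barium Swallow, PAS scores are assigned per consistency. Table 1 offers up to four items to a child aged 1 to 18 years.

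**The concern.** Selection is written into the plan where none is needed. With only five covariates, all named in advance, the data need not decide which enter. When they do, the terms that survive are those that looked strongest in this sample, and the usual p-values and intervals are computed as if no search had taken place. The intervals come out too narrow, the effects of selected terms tend to be exaggerated, and the model may change with small changes in the data. An open set of interactions widens the search.

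The regression also has a unit-of-analysis problem. Texture can be a covariate only if a child contributes one row per texture, and those rows are not independent. Treating them as independent would in general make standard errors too small for covariates that are fixed within a child, such as age and gender.

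The sound tests are a separate matter. Sounds called significant may be read as signs of aspiration, and the stated rule admits false ones at a rate that should be visible to the reader.

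**Working it through.** The plan gives no error rate for the secondary aim, so there is no figure of its own to reproduce. The 108 per group and 216 in total from the Sample size section serve only as simulation sizes.

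**A. Selection among the covariates**

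Inputs from Statistical analyses: five covariates, screen at 0.15, significance level 0.05. Assumption: 0.05 is also the stepwise entry level, since no other is given.

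1. Main effects only, all null and independent: 1 − 0.95^5 = 0.226, or about 23%. The screen does not lower this, because a term with p < 0.05 has already passed 0.15.
2. All ten two-way interactions also candidates (5 × 4 / 2 = 10, so 15 terms): 1 − 0.95^15 = 0.537, or about 54%.
3. Check by simulating forward stepwise logistic regression under the null. Assumptions: binary predictors, 30% OPA prevalence, one row per child, 500 runs per size.

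| Children | Five main effects, 0.15 screen | Five main effects + ten interactions |
|---|---|---|
| 108 | 24.0% | 54.6% |
| 216 | 22.8% | 56.0% |

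4. Narrower reading, with interactions considered only between covariates that passed the screen. At least two of five pass in 1 − 0.85^5 − 5 × 0.15 × 0.85^4 = 1 − 0.444 − 0.392 = 0.165 of null analyses. The expected number of eligible pairs is 10 × 0.15^2 = 0.225. Tested at 0.05, they add at most about 0.225 × 0.05 = 0.011, taking 23% to about 24%.

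The range is therefore about 23% to 54%, depending on which interactions are candidates.

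**B. Rows within child**

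The outcome is recorded per texture, a child can contribute up to four textures (Table 1), and texture is a covariate. The article gives no within-child correlation, so no size can be attached to this.

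**C. The sound tests**

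Table 2: 9 + 9 + 9 = 27 entries. The pre- and post-swallow lists are identical, so there are 9 + 9 = 18 distinct descriptors.

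1. Expected false positives if no sound is associated: 27 × 0.05 = 1.35, whatever the correlation.
2. Chance of at least one under independence: 1 − 0.95^27 = 0.750. Counting only the 18 distinct descriptors: 1 − 0.95^18 = 0.603.
3. With equal pairwise correlation between the 27 test statistics (simulated; the correlations are assumptions):

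| Correlation | 0 | 0.2 | 0.3 | 0.5 | 0.7 | 0.9 |
|---|---|---|---|---|---|---|
| At least one false positive | 75% | 69% | 63% | 48% | 33% | 17% |

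4. If six entries were real (wet breathing, coughing and throat clearing, each pre and post; an assumption), 21 null tests remain: 1 − 0.95^21 = 0.659 under independence, with 21 × 0.05 = 1.05 expected.

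**The case against.** Four points can be made for the plan.

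- **The aim is descriptive and secondary, and handling of multiplicity may sit in an analysis plan not shown here.** This has force for the sounds: a missing adjustment in a condensed article is weak ground, and an exploratory label would be an acceptable answer. It does not reach the stepwise procedure, which the article states outright.
- **The large figures are upper-end values.** This stands. The 75% needs independent tests and no real association. Table 2 repeats descriptors across phases, includes the near-opposites coordinated and uncoordinated, and lists respiratory sounds likely to occur together; the text beneath it cites earlier evidence for wet breathing and cough. The 54% needs all ten interactions to be candidates. Neither should be read as the expected result.
- **Five covariates tested in one model at 0.05 each would also give about 23% for at least one false finding.** This is true, and the remedy does not lower that figure. What it restores is the nominal error rate and interval for each covariate, all five reported whatever their result, and no open search for interactions.
- **The trial's influence on practice rests on the primary aim.** This also stands.

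A reader might go further and infer that the stepwise model selects sounds, so that spurious auscultation signs of aspiration are very likely to come out of it. The article does not support this. The sounds go to chi-square tests; the regression names five covariates and no sound. The screening sentence does speak of all variables without limit, which leaves some doubt. If the 27 sounds did enter, null simulations select at least one in about 72% to 76% of runs. That depends on a reading the text does not establish.

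**Conclusion.** The point holds, mainly for the regression. A p < 0.15 screen followed by forward stepwise selection with unnamed interactions is prescribed for five covariates that could simply be fitted together, and inference after it is anti-conservative. With all covariates null, the chance of at least one false term is about 23% for main effects and up to about 54% if all ten two-way interactions are candidates. Both figures assume independent terms and entry at 0.05. Correlation between rows of the same child is a further defect of unknown size.

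The unadjusted sound tests are a separate and lesser point: 1.35 false positives expected if no sound is associated, with a chance of at least one that is 75% at most and falls as the sounds become correlated. The article does not establish that false entries in the sound list are the likely outcome. Nothing here touches the comparison of CFE + CA with CFE. The change should be made, but the trial's main conclusion does not depend on it.

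**What to change.** - **Covariates.** Replace the screen and stepwise steps with one logistic model containing age, gender, texture, method of intake and clinician experience together, with child as the cluster (GEE or a random intercept). Report all five with confidence intervals.
- **Interactions.** Include only those named in advance. If the interaction with the interval to MBS mentioned in the Discussion is meant to be one of them, say so here.
- **Scope.** State that the sound parameters are not candidates in this model, or, if they are, how they enter.
- **Sounds.** Report each of the 27 entries as an odds ratio with confidence interval. Either control the false discovery rate across the 27 (for example Benjamini-Hochberg at 5%) or label the list exploratory.

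The cost is a change of analysis wording; no new data or children are needed. The downside is fewer nominally significant terms.
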